# INCIDENCE AND FACTORS ASSOCIATED TO THE DEVELOPMENT OF POST-INTENSIVE CARE SYNDROME AMONG FAMILY MEMBERS OF INTENSIVE CARE UNIT SURVIVORS: A LONGITUDINAL EXPLORATORY STUDY

## BACKGROUND

The care and treatment of the sickest patients in a hospital setting are often performed within an intensive care unit (ICU). Life-threatening conditions can lead to mortality rates between 15-20% among ICU patients. Nonetheless, the technical and scientific evolution in the care of ICU patients over the last two decades has radically improved the clinical practice with a decrease in-hospital mortality rates. This increase in survivorship, however, has been associated with several cognitive, psychological, and physical impairments among ICU patients after discharge. Former critically ill patients can experience serious disability and frailty, leading to increased dependence on their caregivers. ICU survivorship has become a new challenge for critical care medicine and public health.

For family members, admission to an ICU is often a stressful and overwhelming experience due to the sudden onset of the critical illness, the risk of death of the patient, and the adoption of a substitute decision-making role. Besides, other stressors may arise for family members such as an unfriendly technological environment, restrictive visitation policies, and low-quality communication with ICU staff. In this scenario, family members may experience significant psychological distress in terms of anxiety (42-80%), depressive (16-90%), and posttraumatic stress disorder (PTSD) symptoms (57%) during admission and may persist, along with other negative outcomes, even 12 months after ICU discharge.

In 2010, the Society of Critical Care Medicine coined the term Post Intensive Care Syndrome (PICS) to refer to any *"new or worsening impairment in physical, cognitive, or mental health status arising and persisting after hospitalization for critical illness"* to raise awareness of the growing body of evidence regarding the long-term sequels of critical illness. PICS prevalence is estimated to affect between 50-70% of ICU survivors. As an extension of this construct, the Post Intensive Care Syndrome – Family (PICS-F) comprises psychological, physical, cognitive impairments, and social consequences that may arise after an ICU stay among family members. Both PICS and PICS-F are now being recognized as a public health burden with substantial associated costs. Despite the increased awareness in PICS-F, evidence to date has focused on the incidence of PICS-F impairments and to a lesser extent, to explore PICS-F related factors. A summary of the evidence on each of the PICS-F impairments, social consequences, risk factors, interventions, and proposed novel factors to be explored in this study is presented below:

## PICS-F Psychological Impairments

Within PICS-F impairments, psychological sequelae are the most investigated and have been associated with the use of psychotropic medication in up to 32% of family members who start these medications after ICU admission and 40% seeking healthcare professionals for emotional problems. In a systematic review including 22 studies published until 2018, family members of ICU survivors reported a variable incidence of anxiety (4%-94%), depressive (2%-80%), and PTSD (3%-62%) symptoms after ICU discharge. The only published study conducted in Chile showed an incidence of 22.9% of PTSD symptoms 2 months after hospital discharge, which resembles subjects who endured the 2010 earthquake in Chile.

Recently published studies have shown similar results. In a single-center study, family members reported 30.6% of anxiety symptoms, 25% of depressive symptoms, and 11% of PTSD symptoms 2 months after ICU discharge. In a small study involving 62 family members, PTSD symptoms were highly prevalent (69.4%) 3 months after ICU discharge. In a multicentric study, Milton et al. reported a prevalence of 8% of anxiety symptoms, 15% of depressive symptoms, and 21% of PTSD symptoms among family members 3 months after ICU discharge. In a longitudinal study with measures at 1, 3, 6, and 12 months after ICU admission, an initial high prevalence of PTSD symptoms (36.3%) decreased over time (24.5%, 21.5%) but increase in the last evaluation (23.6%). Another longitudinal study that involved 221 family caregivers found high levels of PTSD symptoms in 54% of the sample with a trend to reduction during the first 6 months after ICU discharge.

During the current COVID-19 pandemic, Azoulay et al. reported a higher prevalence of anxiety (41% vs 34%), depressive (31% vs 18%), and PTSD (35% vs 19%) symptoms were observed 3 months after ICU discharge among family members of COVID-19 patients, compared to their non-COVID-19 counterparts. In another multicentric study, anxiety, depressive, and PTSD symptoms were experienced at 3- and 12-months post ICU discharge by 31.6% - 29%, 28.3% - 22.8%, and 29.6% - 20.2% of family members of COVID-19 survivors respectively. Overall, the variability in the prevalence of PICS-F psychological impairments could be attributed to the diversity of questionnaires utilized, cut-off values to

establish caseness, and the specific moment in which the questionnaires were applied. Despite this heterogeneity, the prevalence of PICS-F psychological impairments remains higher than in the general population, including the Chilean population during the COVID-19 pandemic.

### **PICS-F Physical & Cognitive Impairments**

Compared to PICS-F impairments, physical impairments among family members of ICU survivors have received little attention. Among family members of former ICU ventilated patients, a significant decline in physical health was reported 6 months after hospital discharge. Similarly, clinically significant fatigue was observed in 43%-53% of ICU family members 4 months after hospital discharge. Likewise, these caregivers reported a worsening in depressive symptoms, health risk behaviors, burden, and sleep quality. In the study of Fumis et al., family members showed a decline in physical health 1 month after ICU discharge with a return to baseline levels at 3 months. Other studies have shown mixed results with a small trend to minimal changes in the physical health of family members of ICU survivors.

Although cognitive impairment is common among ICU survivors and ranges from 30% to 80% after hospital discharge, studies exploring the potential impact of critical illness on family members' cognitive function are missing. Significant cognitive impairment is unlikely to be prevalent among family members during ICU admission since they must assume a surrogate decision-making role and frequently communicate with the ICU team. Furthermore, after hospital discharge caregiving tasks are unlikely to be assumed by a relative with relevant impairment in cognition. However, chronic exposure to psychological stress is associated with poorer cognitive function and an accelerated cognitive decline. Considering the high prevalence of psychological impairments among family members of ICU survivors, some form of cognitive impairment may be present, particularly in older family members of ICU survivors.

### **PICS-F Socioeconomic Consequences**

Despite not being included in the PICS/PICS-F original definitions, socioeconomic burden during and after a critical illness has been described among family members of ICU survivors. Socioeconomic consequences among family members of ICU survivors have been described in terms of loss of employment, financial issues/burden, lifestyle interference, challenge to family dynamics, exacerbation of chronic health conditions, and a decrease in their health-related quality of life. In a small study, 70% of family members expressed some form of financial worry during and after ICU discharge. Likewise, in the study of Swoboda and Lipsett, 45% of family members reported economic issues related to basic needs, housing, and medical care. Moreover, 1 year after ICU discharge, 36.7% of these family members had to move to a less expensive place, delay educational plans or medical treatment, leading to bankruptcy. In secondary data analysis, 48.5% of the family members reported serious financial stress at 3 months and 38.5% at 6 months after ICU discharge with a direct effect on symptoms of anxiety and depression.

### **Factors Associated with PICS-F**

Despite being a multidimensional construct, PICS-F impairments (psychological, physical, and cognitive) have been mostly explored separately with psychological impairment-related factors, being the most reported. Family member-related factors for PICS-F psychological impairments include younger age, female gender, lower educational level, relationship to the patient, lower financial status, history of anxiety and/or depression, rural residence, and ethnicity. Besides, being in a decision-making position, poor communication with the ICU health team, lower educational level, and having a loved one who was close to death have been associated with PICS-F. Concerning patient-related variables, severity of illness, prolonged ICU stay, older age, hospital readmission, and patient disposition at discharge (e.g., home vs assisted care facility) have been reported to be associated with PICS-F psychological impairment. Data on risk factors impacting remaining PICS-F impairments is scarce with discharge to home (vs care facility) being associated with significant fatigue (PICS-F physical) 4 months after ICU discharge.

### **PICS-F Interventions**

Regardless of the awareness of the increased impact and prevalence of the PICS-F, studies reporting interventions are few with heterogeneous results. Furthermore, they have exclusively focused on PICS-F's psychological impairments. Interventions conducted in the post-ICU period are noticeably less than those delivered during the ICU stay. For instance, a multidimensional rehabilitation manual with an emphasis on relaxation and coping strategies plus biweekly phone calls showed no effect on anxiety, depressive, or PTSD symptoms neither at 2 nor at 6 months after ICU discharge. Likewise, the provision of emotional and instrumental support, as well as instrumental case management services, reported no improvements at 2 months post-hospital discharge in caregiving burden, depressive symptoms, or physical health.

Recently published interventions have shown a trend towards positive results. In a before-and-after study, the participation of family members in patient care showed a significant decrease in PTSD symptoms but no effect on depressive symptoms 3 months after ICU discharge. A pilot intervention based on the delivery of cognitive-behavioral therapy via a smartphone app reduced PTSD symptoms in ICU family members 2 months after discharge. Family members' participation in the writing of a diary for the ICU patient showed no significant differences in anxiety, depressive, and PTSD symptoms 3 months after ICU discharge. To summarize, the dissimilar effectiveness observed in PICS-F interventions, particularly those centered on psychological impairments, suggests that PICS-F is a construct that is still not been fully understood and relevant factors may be missed.

### **Psychosocial Resources**

PICS-F literature is focused on family members' psychological distress. Nonetheless, psychological distress can be described as the emotional suffering product of the imbalance between stressors and psychosocial resources. Described as stress buffers or protective factors, psychosocial resources such as perceived social support, resilience, or coping styles have been widely studied among caregivers of different populations but to a lesser extent among caregivers of ICU survivors.

Perceived social support (PSS) refers to the perception of the availability of the different types of resources (e.g., instrumental, psychological, informational) by the subject's close social networks such as family or friends. Different mechanisms are proposed to explain PSS buffer properties on stress. First, the perception that others can deliver the required resources could result in appraising a situation as less stressful. Second, those who receive support may buffer the impact of stress by providing solutions to problems, decreasing the apparent relevance of the problem, by giving a distraction from the problem, or by contributing to healthy behaviors.

Studies exploring PSS among ICU family members are limited with heterogeneous results. During the ICU stay, PSS has been negatively associated with anxiety and depressive symptoms. On the contrary, PSS showed no buffer effect on perceived stress or fatigue severity. Then, ICU family members with higher PSS informed lower depression levels, higher psychological well-being, and mental health 1 year after ICU discharge. In the study of Azoulay et al., family members with higher satisfaction with their social support reported a lower risk to develop PTSD symptoms 3 months after ICU discharge (OR= 0.82, 95% CI 0.74-0.90). Conversely, in a sample of 71 caregivers of ICU survivors in Australia, PSS was not associated with caregiver burden nor self-efficacy 3 months after hospital discharge.

Next, resilient individuals often use different coping strategies (e.g. positive appraisal, benefit finding) to manage negative emotions related to stress. ICU family members with high resilience may have an increased mental strength that improves their ability to recover after difficulties such as the patient's critical illness. In a study involving 171 family members, fewer symptoms of anxiety, depression, or PTSD were observed among resilient family members during their ICU stay. Similarly, resilience was found to be a protective factor against psychological distress at ICU discharge. To date, only one study has explored resilience in the post-ICU period showing that resilient family members of ICU survivors experienced fewer symptoms of anxiety, depression, PTSD, and caregiver burden after ICU discharge. The limited evidence to date suggests a protective role of resilience during the ICU stay of family members that should be explored on PICS-F impairments, after hospital discharge.

### **Family Satisfaction**

During the ICU stay of the patient, family members experience a specific group of needs that influence their experiences of the patient's critical illness. Family satisfaction is the extent to which the needs and expectations of family members are met by healthcare providers during their ICU stay. As a complex and multidimensional construct, family satisfaction comprises the evaluation by family members of key elements of the ICU experience such as communication with healthcare providers, emotional support, closeness to the patient, ICU environment, decision-making involvement, and nursing care of the patient.

A negative association has been reported between family satisfaction and symptoms of anxiety and depression during ICU stay. Moreover, some studies have shown that a worst ICU experience (measured as family satisfaction) may influence post-ICU/hospital outcomes such as PICS-F's psychological impairments. In a small study, family satisfaction and communication with ICU staff were negatively associated with depressive and PTSD symptoms 2 months after ICU discharge. Likewise, low levels of family satisfaction during ICU stay have been associated with higher levels of anxiety, depressive, and PTSD symptoms 3 months after hospital discharge. Then, higher levels of key family satisfaction attributes such as satisfaction with care and decision-making involvement were associated with less risk of depression 3 months after ICU admission. Although the role of family satisfaction in other PICS-F

impairments (e.g., physical, cognitive) is unknown, meeting the needs of family members during and after their stay in the ICU could decrease the negative impact of PICS-F on family members as caregivers.

### Caregiver burden

Up to 80% of the ICU family members become informal caregivers after the patient's hospital discharge. Caregiving is often described as a stressful process that can lead to a significant and multidimensional burden. Caregiver burden (CB) comprises the physical, psychological or emotional, social, and financial problems associated with the care of an impaired person. CB has been extensively studied in caregivers of patients with different conditions but to a lesser extent on family members who provide care to ICU survivors. During the ICU stay of the patient, family members assume a partial caregiving role such as emotional support or surrogate decision-making. However, after hospital discharge, frailty and dependency may arise leading to an increase of caregiving tasks.

Current evidence suggests that being a caregiver of an ICU survivor imposes an elevated burden and strain on family members. In one study, 16% of caregivers reported a high CB and it was positively associated with anxiety and depressive symptoms, but not with PTSD symptoms. In another study, 53% of caregivers experienced high CB with a positive association with anxiety, depressive, and PTSD symptoms as well as with sleep disturbances and poor quality of life. Comini et al. reported a high percentage of caregivers with critical levels of burden. Remarkably, although survivors' global condition improved 6 months after discharge, caregiver strain remained high and the percentage of caregivers needing support tended to increase. In another study, a positive association between CB and depressive symptoms was reported 3 months after ICU admission. Also, a higher CB has been associated with worse mental health and an elevated risk of psychological symptoms 3 months after ICU discharge. Although the association between CB and PICS-F psychological impairment on caregivers of ICU survivors has been reported, the relationship with family member-related variables measured during ICU stay (e.g., psychological distress) remains unclear. Besides, the study of a potential association between CB and PICS-F physical and cognitive impairments is warranted due to the possible conceptual overlap between CB and PICS-F.

### Theoretical Framework

To provide a conceptual organization of the current and potential variables that may be influencing PICS-F impairments, this study will employ an adapted version of the *Pearlin's Caregiver Stress Model* (CSM). In brief, the CSM aims to explain the occurrence of negative outcomes among caregivers (e.g., depression, anxiety, cognitive disturbances, etc.) based on the interaction of the background and contextual factors (family member and patient-related), primary stressors (objective and subjective indicators), and secondary strains (role and intrapsychic). Besides, the relationships between the CSM elements are mediated by psychosocial resources (coping or social support).

In this study, the negative outcomes will be PICS-F impairments (psychological, physical, or cognitive) that are influenced by contextual factors and primary stressors (psychological, physical, and cognitive) experienced by family members during ICU admission/stay and after hospital discharge. Then, secondary stressors can contribute to PICS-F impairments either during the ICU stay (family satisfaction) or after hospital discharge (caregiver burden). In both scenarios, psychosocial resources (social support and resilience) may buffer the primary stressors, secondary stressors, and outcomes. Figure 1 presents the proposed modified version of the CSM model for PICS-F impairments for this study.

[figure not shown]

**Figure 1.** Caregiving Stress Model adapted to Post Intensive Care Syndrome – Family impairments.

**Research questions:** The research questions that will guide the study are: In a sample of family members of ICU survivors of a public hospital in Chile:

- 1) what is the incidence rate of each PICS-F impairment at three and six months after hospital discharge?
- 2) what are the contextual factors, primary stressors, secondary stress, and psychosocial resources associated with each PICS-F impairment at three and six months after hospital discharge?
- 3) If family satisfaction or caregiver burden is associated with PICS-F impairments, to what extent do they contribute to these outcomes at three and six months after hospital discharge?

**Objective:** The aim of this study is two-fold, one cross-sectional and one longitudinal aim.

(1) To determine the incidence of each PICS-F impairment (psychological, physical, and cognitive) among family members of ICU survivors of a public hospital in Chile.

(2) To identify factors, during ICU stay and after hospital discharge, associated with the PICS-F impairments among family members of ICU survivors of a public hospital in Chile.

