The incidence of each PICS-F impairments (psychological, physical, and cognitive) at T3 and T4, will be determined by classifying subjects according to the proposed cut-off scores. The number of subjects showing a given PICS-F impairment will be divided by the total number of subjects at the specific point of the study. Then, to analyze factors associated with PICS-F impairments, bivariate and multivariate analyses will be conducted. Cross-sectionally, Chi-square or Fisher's exact test will be applied in case of analyzing two or more categorical variables. In the case of two continuous numerical variables, Pearson or Spearman correlation test will be used. If one dependent variable is continuous normally distributed and the independent variable is categorical, then a t-test (two groups) or ANOVA test (three or more groups) will be applied; if the dependent variable is non-normally distributed, Mann-Whitney U test (two groups) or Kruskal-Wallis test (three or more groups) will be applied. Bivariate analyses, along with factors identified in the literature, will help to identify potential independent variables for multivariate models.

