Given that this study considers more than one measurement (repeated measures) over time, this information should be considered as correlated within-subjects. Therefore, to analyze variables associated with the PICS-F impairments over time, panel or longitudinal analysis will be used. First, graphical methods, such as panel line plots, will be used to visualize the trend and variation between and within-subjects over time. This analysis will be useful for determining some important covariates and the regression models to be included and applied afterward. Second, the strength of outcome correlation should be defined to decide the regression methods. In this scenario, and considering the nature of the outcome, generalized linear mixed models (GLMM) will be used. Contextual factors (family member and patient features) of each subject will be considered fixed effects, but random effects will be included because it is expected that the outcome in each time and for each subject will vary. Given that the outcome is measured as a dichotomous variable, the family will be binomial, and the link function is expected to be logit. Then, the model will be built starting with a large model and trimming it down according to statistical significance but also based on the proposed theoretical model (CSM). The initial models proposed for this study are presented in Table 1.

If family satisfaction (FS) or caregiver burden (CB) is associated with any of PICS-F impairments at T3 and/or T4, GLMM with and without the selected secondary stressor will be fitted to analyze the extent of this association. First, FS measured at T1 will be added to models 1-4 while the FS measure at T2 will be included in models 5-8. Similarly, CB measured at T3 will be included in models 9-20 while the T4 measure of CB will be added to models 17-20. The original model without a secondary stressor will be contrasted

with the same model plus the secondary stressor (either FS or CB). Scores such as Akaike Criterion and likelihood ratio tests will be performed and residual plots will be obtained. Also, 95% confidence intervals will be reported and a  $p$ -value  $< .05$  will be considered statistically significant. All statistical analyses will be conducted in R, using the applicable packages.

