**Table 1. Variables and generalized linear mixed models to explore PICS-F impairments**

| Independent Variables |                                                                                             |                                                                                                            |       |       |          |      |          |      | Dependent Variables                          |                |          |      |
|-----------------------|---------------------------------------------------------------------------------------------|------------------------------------------------------------------------------------------------------------|-------|-------|----------|------|----------|------|----------------------------------------------|----------------|----------|------|
| Model #               | T 1 - ICU admission                                                              |                                                                                                            |       |       |          |      |          |      | T 3 & T 4 a |                |          |      |
|                       | Patient                                                                                     | Family member                                                                                              | PHQ-4 | IES-6 | mMOS-SSS | BRCS | SF-36 VT | MEFO | PHQ-4                                        | IES-6          | SF-36 VT | MEFO |
| 1                     | Age, SOFA, COVID-19 diagnosis, days since ICU admission, BI                                 | Age, gender, education,                                                                                    | X     |       | X        | X    | X        | X    | X                                            |                |          |      |
| 2                     |                                                                                             | kinship, MHA, previous ICU                                                                                 | X     |       | X        | X    | X        | X    |                                              | X              |          |      |

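### Every multivariable model in Table 1 places contextual factors beside possible mediators, so research question 2 gets no mutually adjusted estimate of their overall association with PICS-F

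*Protocol*

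**What the plan says.** The Theoretical Framework section poses research question 2 as "what are the contextual factors, primary stressors, secondary stress, and psychosocial resources associated with each PICS-F impairment at three and six months" after hospital discharge; specific aim 3 repeats it. The same section describes the impairments as outcomes "that are influenced by contextual factors and primary stressors (psychological, physical, and cognitive) experienced by family members during ICU admission/stay" and after discharge. It also says that psychosocial resources mediate the relationships among the elements of the stress model.

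Under Statistical analyses, "to analyze factors associated with PICS-F impairments, bivariate and multivariate analyses will be conducted". The bivariate part comprises chi-square or Fisher tests, t-tests or ANOVA, rank tests and correlations. It has a second use: "Bivariate analyses, along with factors identified in the literature, will help to identify potential independent variables for multivariate models".

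For the mixed models, "the model will be built starting with a large model and trimming it down according to statistical significance"; the sentence goes on to name the theoretical model as a second guide, and the models in Table 1 are called initial ones. In models 1-4 the patient variables are "Age, SOFA, COVID-19 diagnosis, days since ICU admission, BI". The family variables are age, gender, education, kinship, mental-health antecedents, previous ICU experience, income and employment. These stand beside T1 PHQ-4, mMOS-SSS, BRCS, SF-36 VT and MEFO. The only comparison of nested models described adds family satisfaction or caregiver burden.

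**The concern.** Age, gender, education, kinship, mental-health antecedents and previous ICU experience exist before any study questionnaire is filled in. If such a factor raises distress or fatigue in the ICU, or lowers perceived support, and these in turn raise the risk of impairment at 3 or 6 months, then the scores lie on its path to the outcome. Conditioning on them removes that path from the factor's coefficient. Trimming by significance can then keep the score and drop the factor behind it.

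The factors concerned are ones the protocol itself takes from the literature: "Family member-related factors for PICS-F psychological impairments include younger age, female gender, lower educational level, relationship to the patient, lower financial status", among others. They can also be known when the patient is admitted. A small or absent adjusted association could be read as a local contradiction of that literature when it comes from the model specification. The protocol does not say whether question 2 means the overall association or only the part that bypasses the scores.

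**Working it through.** **1. The plan's own figures, used as inputs.** Initial size: 1.96² × 0.20 × 0.80 / 0.05² = 245.9, so 246 (the protocol states 247). Finite-population step: 600 × 247 / (600 + 247) = 174.97, so 175. Losses: 175 / (1 − 0.40) = 291.7, so 292. The stated figures reproduce to within one. With 175 analysed at 20% incidence, 0.20 × 175 = 35 cases are expected.

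**2. What each model in Table 1 conditions on.**

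| Models | Scores entered beside the contextual factors |
|---|---|
| 1-4 | T1 scores (no IES-6) |
| 5-8 | T2 scores, including IES-6 |
| 9-16 | T3 scores, listed under a T3 outcome heading |
| 17-20 | T4 scores, with T4 outcomes |

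That is 4 + 4 + 8 + 4 = 20 models, of which none holds contextual factors alone. The layout for models 13-16 is hard to read in the extracted table, but those rows also carry symptom and resource scores, so the count is unaffected.

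**3. What conditioning does to the odds ratio.** The protocol gives no effect sizes, so all effects here are assumptions. Let X be a binary factor with 50% prevalence and M = a·X + N(0,1) a distress score. Let logit P(impairment) = i₀ + b·M + c·X, with i₀ set to give 20% incidence. There were 1,000 samples of n = 175 per setting; entries are median odds ratios for X.

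| a (SD) | b (log-odds per unit of M) | c = 0: without M / with M | c = 0.4: without / with | c = 0.8: without / with |
|---|---|---|---|---|
| 0.5 | 0.8 | 1.44 / 1.00 | 2.10 / 1.50 | 2.99 / 2.22 |
| 0.5 | 1.2 | 1.61 / 0.95 | 2.28 / 1.51 | 3.32 / 2.34 |
| 0.8 | 0.8 | 1.82 / 1.01 | 2.63 / 1.51 | 3.86 / 2.29 |
| 0.8 | 1.2 | 2.28 / 1.04 | 3.09 / 1.52 | 4.41 / 2.26 |

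The odds ratios with M recover the direct effect put in: exp(0) = 1.00, exp(0.4) = 1.49, exp(0.8) = 2.23. So the full model estimates the direct part, and the path through M is gone from it.

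**4. What the bivariate tests cover.** They contain no score, so they keep the whole association. They also contain no second contextual factor, so gender is not separated from kinship, nor education from income. The simulation has one factor and cannot size that gap.

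**The case against.** Three stronger readings are tempting, and the protocol does not support them.

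- A reader might infer that contextual factors are judged only in score-adjusted models. They are not: the bivariate analyses are a stated route to associated factors as well as a screen.
- A reader might infer that a factor working through distress will be reported as unrelated. Nothing in the protocol says that a trimmed factor is to be declared unassociated. Theory also guides the trimming, the models are initial, and under partial mediation an odds ratio of 1.5-2.3 remains in the table above.
- A reader might take the fall in detection as a loss to the plan. In the simulation the share with p < .05 falls from 16-57% to 5-6% under full mediation and from 46-94% to 13-45% under partial mediation. But the analysis without the score is in substance the planned bivariate test. In three further assumed settings a plain chi-square test detected the factor in 53%, 83% and 45% of samples, against 51%, 83% and 41% for the single-factor logistic model. Those contrasts compare two analyses that are both planned.

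Timing also limits the point. Scores from the ICU stay itself enter models 1-4 only; T2 follows ICU discharge, and models 9-20 use post-discharge scores. SOFA and days since admission are not clearly earlier than the T1 scores.

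Finally, question 2 speaks of association without saying overall or direct, and the study is exploratory. No hypothesis concerns contextual factors, and hypothesis 3 names them as controls, for which full models are suitable. A statistical analysis plan that is not shown might order the blocks. All this lowers the weight of the point. It does not supply the missing estimate: question 2 and aim 3 name contextual factors, and the protocol's own list of models has no mutually adjusted model of them free of the scores.

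**Conclusion.** The point holds as a gap in the model list. None of the 20 multivariable models estimates contextual factors without possible mediators beside them. The adjusted odds ratio of a pre-existing factor is therefore the part not passing through the measured scores, and a factor acting mainly through these may be attenuated or trimmed out. The bivariate tests show the unadjusted association; nothing planned gives the association adjusted for the other contextual factors.

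The illustrated shift is from an odds ratio of 1.4-2.3 to about 1.0 under full mediation, and from 2.1-4.4 to 1.5-2.3 under partial mediation. It rests on assumed effects, a single score and a single factor. The distance between the bivariate result and a contextual-only model is not quantified. The sample size is not affected. This is a worthwhile, cheap improvement and does not show that the plan would miss these factors.

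**What to change.** In Statistical analyses and Table 1, enter variables in the order of the caregiver stress model: patient and family contextual factors only, then primary stressors, then psychosocial resources, then the secondary stressor. State that:

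- question 2 and aim 3 are answered for contextual factors from the first block, with 95% confidence intervals;
- full-model odds ratios for contextual factors are the part not passing through the measured scores;
- removal of a factor from the full model is not read as no association.

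For factors that precede admission, the first block of models 1-4 is the natural source, because the contextual lists in models 9-20 also hold later items such as readmission and caregiving hours. The full models stay for hypotheses 2 and 3.

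The cost is wording, a few extra fits on data already collected, and two odds ratios per factor to explain. The first block of models 1-4 still holds 5 + 8 = 13 variables for about 35 cases (35 / 13 = 2.7 per variable, against 35 / 18 = 1.9 with the five scores), so its intervals will be wide and should be presented as such.
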